### Ethics and dissemination

Changes to the study protocol are documented in amendments and submitted for approval to the SWSLHD HREC. After completion of the trial, the principal investigator will report on the results of the main study and submit a manuscript to a peer-reviewed medical journal. Supplementary analyses will be reported separately. On study completion, data will be made available upon request.

## Discussion

The REMOTE CONTROL trial will be the first non-inferiority randomised controlled trial, powered to evaluate maternal and foetal outcomes conducted within the Australian healthcare system. A composite foetal events outcome was chosen as the primary outcome, as this represents a definitive end-point relevant to clinicians, patients and the healthcare system. If foetal and secondary outcomes from this study are similar with the institution of remote monitoring, there are major potential benefits to patients and the healthcare system. Through reducing the travel costs, clinic visits and waiting times, it is likely to lead to improved compliance for all patients. In addition, it could improve delivery of care to vulnerable populations in rural and remote communities in Australia, which has unique geographic and social considerations.

The trial is designed to be a pragmatic non-inferiority randomised controlled trial. The underlying pathophysiology of HDP is not going to be altered by the proposed intervention, and therefore a non-inferiority trial design was opted for.

The participant population will be those deemed to be high risk for developing a hypertensive disorder of pregnancy. It is this group of women who are currently being referred to and monitored in an Obstetric Medicine clinic within our local health district. This leads to additional visits throughout their pregnancy, in addition to routine antenatal care. In this high-risk population, the rate of HDP in a recent study set in South Western Sydney was 33.8%, with the rate of adverse foetal outcomes (intrauterine growth restriction or pre-term delivery) between approximately 15–17% (4). Therefore, the high incidence of HDP and foetal adverse outcomes in this population lends itself to an adequately powered study without requiring overwhelming numbers to detect a difference between the groups.

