**Discussion:**

Remote blood pressure monitoring is garnering interest worldwide and has been increasingly implemented following the COVID-19 pandemic. However, robust data regarding its safety for maternofoetal outcomes is lacking. The REMOTE CONTROL trial is amongst the first randomised controlled trials currently underway, powered to evaluate maternal and foetal outcomes. If proven to be as safe as conventional clinic monitoring, major potential benefits include reducing clinic visits, waiting times, travel costs, and improving delivery of care to vulnerable populations in rural and remote communities.

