### Sample size

The sample size calculation is based on the assumption that the composite foetal outcome will be equal in the remote BP monitoring and control groups: a non-inferiority trial. Prior data indicates that the rate of the composite foetal outcome is approximately 31.1%, drawn from a study previously undertaken in the local high-risk pregnant population [4]. Investigators made a reasoned choice about the acceptable difference in adverse foetal outcome and feasibility of the trial. As a result, the non-inferiority margin was defined as a 15% absolute increase or less in the remote BP monitoring group. With a one-sided α of 0.05, the study will achieve a power of 0.80 if 118 women will be included in each trial arm. Furthermore allowing for a 20% attrition rate, 260 participants will be needed in total, 130 participants in each arm.

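### The protocol claims power for maternal as well as foetal outcomes, but its sample size was derived for the foetal composite alone, so maternal power is neither specified nor demonstrated

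*Protocol article*

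**What the plan says.** The claim appears twice. The Discussion paragraph of the Abstract places the trial among the first of its kind "currently underway, powered to evaluate maternal and foetal outcomes". The main Discussion calls it the first non-inferiority trial "powered to evaluate maternal and foetal outcomes conducted within the Australian healthcare system".

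The Sample size section covers one endpoint: "The sample size calculation is based on the assumption that the composite foetal outcome will be equal in the remote BP monitoring and control groups". It gives "the rate of the composite foetal outcome is approximately 31.1" per cent, taken from a local high-risk cohort, and an absolute margin of 15 percentage points. The margin is justified in foetal terms only: "Investigators made a reasoned choice about the acceptable difference in adverse foetal outcome and feasibility of the trial". With one-sided alpha 0.05 and power 0.80 the result is 118 per arm. The recruitment target is 130 per arm.

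The opening paragraph of Methods and the Outcome measures section make the foetal composite primary. Maternal outcomes, including a composite of complications, are secondary (Table 3). The analysis section applies the same risk-ratio model with 95% confidence intervals to binary secondary outcomes and states no non-inferiority criterion for them.

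The main Discussion then makes the expected benefits conditional: "If foetal and secondary outcomes from this study are similar with the institution of remote monitoring".

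**The concern.** A trial is powered for an outcome only in relation to a stated effect or margin, an assumed event rate and an error rate. The protocol supplies all of these for the foetal composite and none for the maternal composite. The claim in the Abstract and the main Discussion therefore conflicts with the Sample size and Outcome measures sections.

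This is more than loose phrasing for two reasons. The Background faults earlier studies for not being powered on maternal, foetal and neonatal outcomes, so the claim presents this trial as filling that gap. On the maternal side, the design as described does not. Second, the trial asks a safety question, and the main Discussion links its benefits to secondary outcomes being similar, without saying how similarity would be judged. A reader told that the trial was powered for maternal outcomes could take a non-significant maternal comparison as evidence of equal maternal safety.

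**Working it through.** **Step 1: reproduce the stated sample size.** Inputs from the Sample size section: p = 0.311 in both arms, margin m = 0.15, one-sided alpha 0.05 (z = 1.645), power 0.80 (z = 0.842).

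n per arm = (1.645 + 0.842)² × 2p(1 − p) / m² = 6.183 × 0.4286 / 0.0225 = 117.8, rounded up to 118.

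Power at n = 118: SE = √(0.4286/118) = 0.0603, and Φ(0.15/0.0603 − 1.645) = Φ(0.844) = 80.1%.

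The stated 118 is fully accounted for by the foetal inputs.

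**Step 2: look for maternal inputs.** The protocol gives no expected rate for the maternal composite, no maternal margin and no maternal power. The 33.8% in the Background and main Discussion is the rate of hypertensive disorders of pregnancy. It is not the rate of the composite of complications in Table 3, and no calculation uses it.

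**Step 3: what 118 per arm could deliver.** The maternal rates (5%, 10%, 20%) and margins (5, 10, 15 points) below are assumptions. True rates are taken as equal, with one-sided alpha 0.05 and the same formula, power = Φ(m/√(2p(1 − p)/n) − 1.645).

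Example at p = 0.10, m = 0.05: SE = √(0.18/118) = 0.0391, and Φ(1.280 − 1.645) = Φ(−0.365) = 36%.

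| Assumed maternal rate | 5-point margin | 10-point margin | 15-point margin |
|---|---|---|---|
| 5% | 55% | 97% | over 99% |
| 10% | 36% | 82% | 99% |
| 20% | 25% | 61% | 89% |

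**Step 4: precision.** Half-width of the 95% interval for the risk difference = 1.96 × √(2p(1 − p)/118):
- at 5%: 1.96 × 0.0284 = 5.6 points
- at 10%: 1.96 × 0.0391 = 7.7 points
- at 20%: 1.96 × 0.0521 = 10.2 points

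**Step 5: with the stated attrition.** A 20% loss from 130 leaves 130 × 0.80 = 104 per arm. Power falls and the intervals widen. At a 10% rate, power becomes 33%, 78% and 98% for the three margins, and the half-width is 1.96 × √(0.18/104) = 8.2 points.

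These are normal approximations. At a 5% rate only about six events per arm are expected (0.05 × 118 = 5.9), so that row is rough. The planned analysis reports risk ratios; the risk difference is used here because the protocol's own margin is absolute.

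**The case against.** The strongest reply is that the trial may well have adequate maternal power. If the protocol's 15-point absolute margin were carried over, power at 118 per arm would be 89% or more at every rate in the table. A 10-point margin would also give 80% or better at rates up to 10%. That stands against the stronger inference a reader might draw, that the design lacks maternal power or could not exclude a large rise in maternal complications. The documents do not support that inference, because they do not say what maternal increase would count as large. Nor do they support carrying the foetal margin over: it was chosen for the foetal outcome, and at an assumed 10% maternal rate it would accept a rise to 25%.

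A second reply is that the priorities are open. The foetal composite is named as primary in Methods, and again in the sentence directly after the disputed one in the main Discussion. Confidence intervals for binary secondary outcomes are already planned. This too is fair, and it limits the point to what is claimed about power.

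A third reply is that nothing commits the investigators to reading non-significance as safety. That is correct: the sentence about similar secondary outcomes is conditional and carries no significance rule. The misreading is a risk created by the wording, not a stated plan.

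**Conclusion.** The statement is wrong as written. It is an internal inconsistency, not a calculation error: 118 per arm is correct for the foetal inputs given. The design specifies 80% power for the composite foetal outcome. For maternal outcomes, power is neither specified nor demonstrated.

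No single figure can be put on maternal power. At 118 per arm, over assumed rates of 5% to 20% and margins of 5 to 15 points, it runs from about 25% to over 99%. The figure depends entirely on a rate and a margin that the protocol does not give. The less assumption-laden statement is about precision: over the same rates the 95% interval for the risk difference would reach about 5.6 to 10.2 points either side, and wider with 104 per arm. A non-significant maternal difference would have to be read against intervals of that width.

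**What to change.** In the Discussion paragraph of the Abstract and in the opening of the main Discussion, restrict the power statement to the composite foetal outcome.

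Qualify the main Discussion sentence about foetal and secondary outcomes being similar. It should say that absence of a significant maternal difference will not be taken as similarity or equal safety, and that maternal conclusions rest on the 95% confidence intervals already planned for binary secondary outcomes.

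If the investigators wish to keep a maternal power claim, they would need to state an expected rate for the maternal composite, a justified margin and the resulting power.

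The wording change needs no more participants and alters no endpoint, sample size or analysis. Its only cost is a more modest claim.

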### Trial status

Recruitment commenced in July 2022, with planned end date of the trial to be September 2023. The protocol is version 2 dated 28th April 2021.

## Data Availability

Full trial dataset will be available to the Coordinating Principal Investigator and site lead investigators. The CSIRO AEHRC team will only be able to access de-identified, grouped data so that they are able to audit the processes, use and feasibility of their application. They will not be involved in the data collection of the study. Deidentified research data will be made publicly available when the study is completed, published, upon ethics approval. The author’s will need to be approached for data to ensure it is appropriately handled. Statistical analysis will occur with commercially available statistical programs, SPSS (version 27).

## Abbreviations

AEHRC: Australian e-Health Research Centre
BP: Blood pressure
CEA: Cost effectiveness analysis
CONSORT: Consolidated Standards of Reporting Trials
CSIRO: Commonwealth Scientific and Industrial Research Organisation
CUA: Cost utility analysis
HDP: Hypertensive disorders of pregnancy
IHPA: Independent Hospital Pricing Authority
IVF: In vitro fertilisation
LDA: Low dose aspirin
MBS: Medicare benefits schedule
mHealth: Mobile health
NICE: National Institute for Health and Care Excellence
PBS: Pharmaceutical benefits schedule
PFA-100: Platelet function analyser-100
QALY: Quality-adjusted life years
SWSLHD HREC: South Western Sydney Local Health District Human Research Ethics Committee
TMG: Trial Management Group
VOI: Value of information
